##### Questionnaires for physicians

All professional health care providers (*n* = 80) will be quantitatively surveyed in cooperation with the OrgValue project of CoRe-Net. OrgValue (Organization & Value) focusses on patient-centeredness and on economic aspects (resources, costs, payment). OrgValue analyzes the health care organizations involved in the care of patients studied in MenDis-CHD using a structured questionnaire to assess their knowledge, attitudes, and experiences concerning patient needs and preferences and barriers associated with MD detection and treatment.

##### Statutory health insurance data (SHI)

Secondary claims data will be provided by four major health insurances of the state of North Rhine-Westphalia in Germany, from 2011 to 2015, for insuree living in Cologne. This SHI data is part of the CoRe-Net-database and will be used for this project (https://www.core-net.uni-koeln.de/index.php/de/core-net-datenbank/). Besides master data (e.g., age, sex, insurance status and period of insurance) information concerning the use of all sectors of care (inpatient and outpatient care, drug prescription, benefits in kind, long-term care) will be available and connectable by a non-identifiable study number. In detail, ICD-10 coded diagnoses from out- and inpatient care, medical services according to the EBM-Code (German physician fee manual), hospital stays with length of stay and OPS-procedures (Operations and Procedures Key), drug prescription with pharmaceutical registration number and linkage to ATC-Code (Anatomical Therapeutic Chemical Classification System) and DDD (Defined Daily Dose Classification), as well as information concerning inability to work (diagnosis, duration) and utilization of long-term care will be provided. For all services, provided SHI cost data will be available. Spatial data (e.g., INKAR: Indicators and maps for area- and town development) could be added.

In a first step, quality and plausibility checks of the SHI-data are performed. In a second step, patients with CHD and MD are identified by their diagnoses, which will be internally validated [44]. Inclusion criteria for CHD patients will be a hospital discharge diagnosis of CHD (ICD 10-GM code I20- I25), for chronic heart failure patients (ICD 10-GM code I11.0, I13.0, I13.2, I50), an outpatient diagnosis in at least two quarters of a or a hospital discharge diagnosis and for MD-patients (ICD 10 GM-code F00-F99, and more specific: F06.7, F32, F33) in one quarters of year or a respective hospital diagnosis. We will apply a cross-sectional design for basic epidemiological data (e.g., frequency of CHD, CHD, and MD, psychotherapy, mortality) and a cohort design for the analysis of care trajectories starting in 2013, allowing a pre-observation period and a follow up of at least 2 years each.

These SHI-data will enrich the empirical part of the study [19] [45] as it allows to compare characteristics of general CHD-population with MD identified in the data to those included into the study and to determine the possible selection bias.

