#### Patients

We intend to enroll adult patients (*n* = 400; 50% women) with angiographically documented CHD treated for stable angina pectoris, acute coronary syndromes, percutaneous coronary intervention, or bypass surgery. Participants must be able to give informed consent and have sufficient German language skills. Exclusion criteria are severe or instable physical or mental conditions (e.g., severe illnesses such as cancer, acute suicidal ideation, delirium, and moderate to severe dementia). Since we are conducting a descriptive and exploratory study, but not a confirmatory one, we did not performed a sample size calculation based on a power calculation. Rather the focus of MenDis-CHD is on vulnerable subgroups. These vulnerable subgroups comprise (1) older female CHD-patients which were underrepresented in past studies, (2) CHD-patients with comorbid mental disorders and/or mild cognitive impairment (expected prevalence of MD and MCI is 30–50%), and (3) CHD-patients with congestive heart failure (expected prevalence of 30% with a left ventricular ejection fraction of < 40% [24]). To obtain a realistic estimate of the health care situation, patients will be recruited in cardiology departments of hospitals, cardiology practices, and rehabilitation clinics.

Thus, the rational for the intended sample size are this estimated frequency of the gender distribution, mental and cognitive comorbidity and patients with congestive heart failure as well as the goal of recruiting in different sectoral areas (hospitals, rehabilitation clinics, and cardiology practices). By this rationale, we aim at a sufficiently large sample sizes to perform the statistical comparison in these vulnerable subgroups. In sum, the recruitment of a total *N* of 400 patients is planned. Thus, we aim to recruit *n* = 200 women, *n* = 130–200 patients with MD or MCI and *n* = 120 with congestive heart failure.

All 400 patients (with and without MD) will take part in the quantitative study. *N* = 20 participants of the patient sample will be invited to join qualitative interviews.

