#### Study population of SHI data

SHI data of patients who are inhabitants of Cologne continually insured between 2011 and 2012 and continually insured or deceased in 2013 through 2015 in one of the four participating health insurance companies - (estimated about 270,000 persons) will be provided.

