#### SHI data

We will provide frequency measures for patients with CHD in general and for those with (1) MD present before the hospital stay and (2) MD documented for the first time, i.e. no hint for MD by diagnosis or drug prescription in the interval of one respective two years before index stay (the MD group will be of main interest). This respective hospital stay serves as an index period, which allows the description of pre and post use of health care services and care trajectories. Besides estimating prevalence for CHD and CHD with comorbidity like MD, the data allows to assess by whom and how patients are treated (specialty of physician group, diagnostic procedures, non-medical therapy, drug prescribing, further hospital stays) and how patients comply with the treatment (adherence to medication regime according to the PDC methodology expressing the percentage of days covered with medication [47, 48]). Absent days at work, early retirement and medical costs will also be analyzed. Predictors for MD treatment related to the information available in claims data will be assessed.

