## Discussion

Data will be generated from multiple sources, including claims data, surveys, interviews and focus groups of professionals, patients, and relatives. Thus, our study design adopts a multi-perspective approach, which combines patients, their relatives and physicians views with in-depth analysis of trajectories, quality of health care, needs and preferences by quantitatively and qualitatively methods. Besides, we are able to gain insight into the general treatment of a non-selective population with CHD and MD by using SHI data.

The value-based concept by Porter [20–22] forms the analytical framework for our project. Consequently, our vision is to create value for the patient paying attention to both quality of health care and costs. MenDis-CHD will provide essential insights into the trajectories of health care, quality of health care, barriers, patient needs and preferences as well as expectations and satisfaction with health care in patients with CHD and MD.

The multi-method and multi-perspective approach of MenDis-CHD will provide data-driven analysis tools to enable care providers to redesign care pathways by proposing value-based changes in care and to understand the barriers to and facilitators of change towards patient-centered care. Restructuring complex care for vulnerable CHD patients is very much needed since there is evidence that these patients are underserved and often get lost in the transition between multi-professional and multi-institutional care providers [51, 52]. This generates unnecessary costs, ill health and thus low value for the patient.

MenDis-CHD has already begun to perform workshops inviting our scientific and practice partners, stakeholders, caregivers, patient and relative representatives to develop specific deliveries and methods for value-based health and social care in highly vulnerable patients with CHD and MD. Moreover, we have built up a representative network of recruitment centers. However, practice will have to show how well we succeed in recruiting patients against the backdrop of a significant reduction in inpatient stays. As already noted, women represent a vulnerable subgroup underrepresented in previous studies. Thus, recruitment will have to additionally show how demanding it is to achieve the targeted sample sizes of female patients.

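### CHD is identified in the claims data by hospital discharge code only, so the planned CHD prevalence describes hospital-coded CHD, and the survey comparison mixes selection with case definition

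*Protocol article*

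**What the plan says.** All references are to the protocol article.

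- **Case definition** (Statutory health insurance data): "Inclusion criteria for CHD patients will be a hospital discharge diagnosis of CHD (ICD 10-GM code I20- I25"). The same sentence gives heart failure a wider rule, "an outpatient diagnosis in at least two quarters of a or a hospital discharge diagnosis", and mental disorders (MD) a wider one still, "in one quarters of year or a respective hospital diagnosis". The section also says that ICD-10 diagnoses from both outpatient and inpatient care will be delivered.
- **Index event** (Outcomes, SHI data): MD is classed as present before the hospital stay or first documented, and that stay is the index period for describing care before and after.
- **Prevalence aim** (same section): "Besides estimating prevalence for CHD and CHD with comorbidity like MD", the data are to show who treats patients and how. Frequency measures are promised for CHD patients in general, and the Statutory health insurance data section lists the frequency of CHD under its cross-sectional design.
- **Benchmark aim** (Statutory health insurance data): the general CHD population with MD found in the claims is to be compared with "those included into the study and to determine the possible selection bias".
- **Survey sample** (Patients): "patients will be recruited in cardiology departments of hospitals, cardiology practices, and rehabilitation clinics". Stable angina is among the qualifying conditions.
- **Description of the claims population** (Discussion): the study can "gain insight into the general treatment of a non-selective population with CHD and MD by using SHI data".

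**The concern.** One case definition serves two purposes with different needs. A dated hospital stay is a sensible anchor for a trajectory cohort. It is not a sensible numerator for CHD prevalence, because a CHD patient with no CHD discharge in the data window cannot be counted however often the outpatient record carries the diagnosis.

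The same gap affects the selection-bias check. A survey patient recruited in a cardiology practice who has had no CHD discharge has no counterpart in the claims reference group. A difference in age, sex, MD frequency or treatment between survey and claims could then be read as selective participation when part of it comes from how CHD was defined.

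The frequency of CHD, the frequency of MD within CHD and the representativeness of the survey are main outputs of the claims component. In a descriptive study their validity rests largely on the case definition.

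**Working it through.** The article states no expected number of CHD cases in the claims data, so there is no planned figure to reproduce. The check is a comparison of the sections, followed by an illustration of size.

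**Step 1: is the hospital-only reading right?** The sentence with the three definitions is incomplete in the heart-failure part, since the period for the two quarters is missing. The CHD clause, however, is complete before the heart-failure clause begins, so the outpatient rule attaches to heart failure. The Outcomes section agrees, because it takes a hospital stay as the index period. No section gives an outpatient criterion for CHD, and none limits the prevalence aim or the survey comparison to hospitalised CHD.

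**Step 2: effect on prevalence.** Let f be the share of CHD patients with a CHD discharge code in the window. If every discharge code is a true case:

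captured prevalence = true prevalence × f, and understatement = 1/f.

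Inputs for an illustration:
- CHD prevalence of 12.3% in men and 6.4% in women (Background);
- about 270,000 insured persons (Study population of SHI data);
- half of them women, and the Background prevalences apply to them (assumptions);
- f from 0.2 to 0.8 (assumption; the documents give no value).

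True prevalence = 0.5 × 12.3% + 0.5 × 6.4% = 9.35%, and 9.35% × 270,000 = 25,245 persons. With 45% or 55% women the count is 26,042 or 24,448.

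| f | Captured prevalence | Persons found | Persons missed | Understatement (1/f) |
|---|---|---|---|---|
| 0.2 | 1.87% | 5,049 | 20,196 | 5-fold |
| 0.4 | 3.74% | 10,098 | 15,147 | 2.5-fold |
| 0.6 | 5.61% | 15,147 | 10,098 | 1.67-fold |
| 0.8 | 7.48% | 20,196 | 5,049 | 1.25-fold |
| 1.0 | 9.35% | 25,245 | 0 | none |

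The two quantities agree only at f = 1. Pooling all five data years, or counting secondary discharge diagnoses, would raise f; the article settles neither.

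**Step 3: effect on the MD share.** If MD is more or less frequent in hospitalised than in other CHD patients by d percentage points, the hospital-only MD share differs from the all-CHD share by (1 − f) × d. As an illustration, take d = 20, with the ends of the article's expected 30–50% range for MD and mild cognitive impairment assigned to the two groups by assumption. The shift is then 16, 12, 8 and 4 points at f = 0.2, 0.4, 0.6 and 0.8. The documents give neither the size nor the sign of d, so this shows sensitivity and is not an estimate of bias.

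**Step 4: effect on the survey comparison.** Hospital-recruited survey patients have a like-for-like claims group. Practice patients have one only if they also had a CHD discharge in 2011–2015. For the rest, selection into the survey and the difference in case definition cannot be separated.

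**The case against.** **The hospital stay has a stated purpose.** Care before and after needs a dated event, and CHD in general can be read as all index patients as opposed to the MD subgroups. This stands for the trajectory cohort. It does not cover the cross-sectional frequency or the explicit prevalence aim.

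**The non-selective description may mean free of consent and participation selection.** That is fair, since the Discussion sets it beside the surveys. The label still needs restricting, because the group is selected on hospital admission.

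**This is a condensed article of an exploratory study.** Operational claims definitions often sit in a fuller document, the article says diagnoses will be internally validated, and no test or sample size depends on this rule. That lowers the stakes. But the article does state a CHD rule, and the stated rule does not fit the stated aims.

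A reader might also infer three stronger things that the documents do not support:

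- *That the selection-bias check is invalid altogether.* Survey patients have angiographically documented CHD, and many treated for acute coronary syndrome, by percutaneous intervention or by bypass will have a discharge code. Being seen in a practice does not mean never having been admitted. The check is misspecified, and it remains usable for the hospital-recruited stratum.
- *That the claims results describe sicker patients with more MD.* This is plausible, but nothing in the documents shows it.
- *That mortality is materially overstated,* because the frame requires persons "continually insured between 2011 and 2012 and continually insured or deceased in 2013 through 2015", which removes leavers but keeps deaths. People who leave and die later are lost too, so deaths are removed along with survivors. No exit rate is given. At most, the rule may modestly overstate mortality.

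**Conclusion.** The point holds for the case definition. Followed as written, the plan would report the frequency of hospital-coded CHD as CHD prevalence and would use that group as the general CHD benchmark for a survey with wider recruitment. The direction for prevalence follows from the rule whenever some CHD patients have no discharge code and discharge codes are accurate. The size depends on f, which the documents do not give: 1.25- to 5-fold for f between 80% and 20%, on assumption alone. The survey comparison is confounded with case definition for practice patients and sound in principle for hospital patients. The effect on MD frequency is undetermined in size and sign. The index-stay cohort itself is not at fault.

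**What to change.** 1. For the cross-sectional frequency and prevalence, and for the comparison with the survey, define CHD as I20–I25 in at least two outpatient quarters or one hospital discharge. This is the rule already used for heart failure. State the period within which the two quarters must fall.
2. Report the hospital-only definition alongside it, so that readers see how far the result depends on the definition.
3. Keep the hospital-only group as the index-stay trajectory cohort and label it hospitalised CHD throughout.
4. Stratify the survey-versus-claims comparison by recruitment setting.
5. In the Discussion, restrict the non-selective description to what the chosen definition supports.
6. Optionally, add one sentence that excluding leavers while keeping deaths may modestly overstate mortality. No new data request is needed for this.

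The cost is a changed case-finding query on outpatient codes that are already part of the delivery, one extra set of tables, and wording. The downside is that outpatient-coded CHD is less certain than a discharge diagnosis, which is why both definitions should be reported.

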Given that adherence to CHD guidelines in physicians is generally low, even when these guidelines predominantly comprise somatic recommendations [16], it is unlikely that general practitioners and cardiologists regularly screen for MD due to typical restraints such as a lack of time and low reimbursement of verbal interventions [12, 17]. However, a systematic review in 2013 showed that depression screening is only beneficial for identifying depressed patients that were not already diagnosed or treated for depression. Also, the accuracy of screening tools seems to be exaggerated by the inclusion of already diagnosed patients and the selective reporting of results from cut-off scores. Following this review, a wide range of routine screening would entail high costs and increase the number of patients using antidepressants. Hence, it is important to not only look at the screening for MD and cognitive impairements but also to look at diagnostic and treatment following the screening [18]. Overall, the status of quality of care in CHD patients with comorbid mental disorders is unknown. Moreover, it is unclear what the trajectories of care of patients with CHD and cognitive impairement are.

In addition, no data on personal preferences, needs, and expectations of patients with CHD and their relatives regarding the detection and treatment of MD have been published. Thus, there is an urgent need to explore the current state of care in patients with CHD and MD to identify relevant factors that are preventing improved care in health care systems.

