##### Clinical questionnaires

The *Hospital Anxiety and Depression Scale* (HADS; [26, 27]) will be used as a screening tool for MD. The HADS is a self-report questionnaire to assess symptoms of depression and anxiety. It contains 14 items, which can be rated on a 4-point Likert-scale. Depression and anxiety sub-scales can be extracted. An anxiety/depression score between 0 and seven is considered ‘negative,’ between eight and ten ‘sub-syndromal positive’ and between 11 and 21 ‘positive’ for depression and/or anxiety. The reliability for the anxiety scale is α = .80, for the depression scale α = .81. The retest-reliability within 2 weeks is α = .80 for the anxiety scale and α = .83 for the depression scale. The construct validity is between α = .06–.08. Cronbach’s Alpha of the HADS is 0.80, and the retest is indicated as α = .80 [28].

The sensitivity and specificity for case detection are around .80 for both scales [28]. HADS-screening will be defined as ‘positive’ if the score is greater or equal to eight. In this case, the *Structured Clinical Interview for DSM-IV* (SKID-I; [29]) will be conducted. The SKID-I is a semi-structured interview to assess psychiatric symptoms and disorders as defined in the DSM IV (*Diagnostic and Statistical Manual of Mental Disorders*; [30]). Lifetime and current diagnosis are assessed for the following disorders: [1] affective disorders, psychotic disorders, disorders through psychotropic substances, anxiety disorders, somatoform disorders, eating disorders and adjustment disorder. The test-retest reliability relevant for this study are within the range of α = .61–.76 for unipolar affective disorders and α = .65–.63 for anxiety disorders [31]. The sensitivity for affective disorders is .53 and for major depression .84. The specificity for affective disorders is .97 and for major depression .91 [32].

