### Procedures

The University Hospital of Cologne (Department of Psychosomatics and Psychotherapy and Department of Psychiatry and Psychotherapy) is the only recruiting site. However, participants will be recruited in cardiology departments (University Hospital Cologne, Department of Internal medicine, Cardiology, Pneumology and Internal Intensive Care Medicine; Cologne-Merheim, clinics of the city of Cologne, Department of Cardiology, Rhythmology and Internal Intensive Care Medicine), patients from two cardiologic rehabilitation clinics (Clinic Roderbirken - Rehabilitation Centre for Heart and Circulatory Diseases; AmKaRe Cologne: out-patient cardiological rehabilitation centre) and from three cardiologic practices (Practice for Internal Medicine, Cardiology, Pneumology, Cologne, [name]; Practice for Cardiology Cologne, [name]; Practice for Cardiology Cologne, [name]). All patients screened for eligibility will be documented in a screening log. Patients who fulfill all inclusion and no exclusion criteria and provide written informed consent will be handed out the quantitative questionnaires and will be asked to participate in the qualitative interviews. If this screening with the HADS and/or the DemTect is positive, a second appointment will be arranged to perform the SKID-I and/or the CERADPlus. All participating researchers (SP and HM) were trained in applying the SKID-I and CERADPlus and are experienced in conducting the interviews with patients and research participants. The subsample of 20 participants, 20 relatives, and 20 physicians will be randomly contacted for a qualitative interview at a third time point. Furthermore, focus groups with 40 physicians will be randomly contacted.

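### The claims-based selection-bias check compares groups whose mental disorders were found in different ways, so for characteristics linked to detection or coding it cannot separate selection from ascertainment

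*Protocol article*

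**What the plan says.** The last paragraph of Statutory health insurance data (SHI) gives the claims data a validation role: they allow the team to "compare characteristics of general CHD-population with MD identified in the data to those included into the study and to determine the possible selection bias". The benchmark is thus the claims group with CHD and MD. The study-side group is given only as those included, with no statement whether this means participants with MD or all participants.

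The same section defines the claims group: "patients with CHD and MD are identified by their diagnoses, which will be internally validated". The criterion is "for MD-patients (ICD 10 GM-code F00-F99, and more specific: F06.7, F32, F33) in one quarters of year or a respective hospital diagnosis".

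In the study, MD is found by research assessment. Patients complete the HADS and DemTect, and after a positive screen "a second appointment will be arranged to perform the SKID-I and/or the CERADPlus" (Procedures; instruments under Clinical questionnaires). No physician record is needed.

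The Background treats detection in routine care as doubtful: "it is unlikely that general practitioners and cardiologists regularly screen for MD". The Abstract lists reasons for non-detection among the things to be explored. The Discussion describes the claims side as follows: "we are able to gain insight into the general treatment of a non-selective population with CHD and MD by using SHI data".

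**The concern.** A person enters the claims MD group only if a diagnosis was coded in routine care. A person enters the study MD group through research instruments, including people whose disorder no physician recorded. The benchmark is therefore conditioned on detection, which is itself one of the study's questions. No step is stated that puts the two sides on a common definition, and the planned validation of claims diagnoses is internal.

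Two errors become possible. A sound sample could be reported as selected because its MD patients are treated less or use fewer services than claims MD patients. Or a sample that over-recruited already diagnosed patients could look reassuringly similar to claims. Treatment rates in claims are also conditional on a recorded diagnosis, which matters if they are read as the care of everyone with CHD and MD.

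**Working it through.** The article gives no figure for this check, so there is nothing to reproduce. The following illustrates its behaviour.

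**From the article.** 130 to 200 study patients with MD or MCI, 400 patients in all (Patients).

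**Assumed.** Detection rates, treated shares, miscoding rates and a two-sided 5% test; the article states none of these. Study MD is taken as true MD. Unless stated otherwise, there is no selection bias and claims contain no false-positive MD.

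**Method.** The count x of study MD patients with the characteristic is binomial with n = 130 or 200 and share p_s. The claims share p_c is treated as fixed. A signal is |x/n − p_c| / √(p_c(1 − p_c)/n) > 1.96, with exact binomial probabilities.

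**(a) Trait unrelated to detection.** With detection equal in those with and without the trait, p_c = p_s. At a share of 0.5 the signal rate is 4.3% (n = 130) and 5.6% (n = 200). There is no artefact.

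**(b) Trait related to detection.** With true share p and detection d1 (trait) and d0 (no trait), p_c = p·d1 / (p·d1 + (1 − p)·d0). At p = 0.5:

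| d1 / d0 | p_c | Signal, n = 130 | Signal, n = 200 |
|---|---|---|---|
| 0.55 / 0.45 | 0.275/0.50 = 0.55 | 22% | 31% |
| 0.60 / 0.40 | 0.30/0.50 = 0.60 | 67% | 82% |

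A two-sample calculation with 2,000 or 10,000 claims MD patients (assumed) gives 20–29% for the first row and 61–81% for the second. At 0.70 / 0.30 (p_c = 0.70) it exceeds 99%.

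**(c) Treatment.** A share d of true MD is recorded, a share t of recorded MD is treated, and unrecorded MD is untreated. Then p_s = d·t and p_c = t, so even random under-detection creates a gap.

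| d | t = 0.3, n = 130 | t = 0.3, n = 200 | t = 0.5, n = 130 | t = 0.5, n = 200 |
|---|---|---|---|---|
| 0.5 | 98% | >99% | >99% | >99% |
| 0.7 | 61% | 83% | 93% | 99% |
| 0.8 | 29% | 47% | 61% | 83% |
| 0.9 | 10% | 15% | 19% | 31% |

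On these assumptions the treated share in claims exceeds that among all MD by a factor t/(d·t) = 1/d: 2.0 at d = 0.5 and 1.4 at d = 0.7.

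**(d) False-positive codes.** If a share f of claims MD cases are false positives and untreated, p_c = t(1 − f). Take d = 0.7, t = 0.5, n = 130, so p_s = 0.35. At f = 0.2, p_c = 0.40 and the signal falls from 93% to 23%. At f = 0.3, p_c = 0.35 and it is about 4%.

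**(e) Masking.** Now let there be real selection. Population detection is 0.7 and t = 0.5, but 90% of the study's MD patients are already recorded. Then p_s = 0.9 × 0.5 = 0.45 against p_c = 0.50, and the signal at n = 130 is 19%. If all were recorded, p_s = p_c and it is about 4%. With no selection it would be 93%. On this characteristic, the more the study over-recruits detected patients, the more reassuring the check looks.

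**(f) Study side read as all 400.** The comparison is then between claims patients who all have coded MD and participants of whom 30–50% are expected to have MD or MCI. The groups differ on MD status by construction.

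**The case against.** A reader might infer that under-detection alone makes the check report selection bias where there is none, or that the plan treats any difference as bias. The article does not support that. It names no test, threshold, decision rule or list of characteristics, and it calls the analyses exploratory. It does not say that the study side is the interview-diagnosed group. Result (a) shows no artefact for characteristics unrelated to detection. The high rates in (c) depend on choosing treatment as the characteristic and on assuming that no unrecorded case is treated.

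Nor does the article say that MD is often undetected. It calls regular screening unlikely, calls the quality of care unknown, and lists reasons for non-detection as something to explore. Error also runs both ways: any F00–F99 code in one quarter can over-include, as in (d), and the HADS gate has a stated sensitivity of around .80, so the study group is not complete either.

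The SHI outcomes are already largely framed as diagnosed or documented MD, and the phrase in the Discussion can fairly be read as meaning free of recruitment selection. A condensed article may also leave the choice of characteristics and subgroups to the full protocol.

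All of this limits the size and reach of the point. It does not remove it. The article names the benchmark and the conclusion to be drawn from it, and that conclusion does not follow from that comparison. Neither available reading of the study side makes it like for like.

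**Conclusion.** The point holds in a limited form. MD is ascertained differently in the two sources and no harmonising step is stated. For characteristics related to being detected or coded, a difference can arise without selection bias and a match can conceal it. For characteristics unrelated to detection, no such artefact arises.

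The size cannot be fixed from the article. Under the assumed detection, treatment and miscoding rates and an assumed 5% test, the false-signal rate runs from about 5% to nearly 100%. It is small when detection is near 0.9 or when false-positive codes offset the gap.

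The patient survey outcomes do not depend on this comparison. What is affected is the claim to determine selection bias, and any reading of claims treatment rates as the care of all people with CHD and MD. Because the change is cheap, it should be made.

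**What to change.** Rewrite the last paragraph of Statutory health insurance data (SHI):

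1. Compare all enrolled CHD patients, with and without MD, with all claims CHD patients on characteristics recorded independently of MD: age, heart failure, cardiac procedures and comorbidity.
2. Stratify this by sex, because 50% women is fixed by design and a difference in sex distribution would say nothing about unplanned selection.
3. Make the comparison mainly for patients with a hospital stay for CHD. The claims definition requires a hospital discharge diagnosis, while the study also recruits in cardiology practices and rehabilitation clinics.
4. For any comparison within MD, use study patients who report a physician diagnosis or treatment of MD, if the health care questionnaire records this (its items are not shown), against claims patients with recorded MD.
5. State that differences between interview- or test-diagnosed study patients and claims MD patients reflect detection and coding as well as selection.

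In the Discussion, describe the claims group as a population with CHD and recorded MD, and report its treatment rates as conditional on a recorded diagnosis.

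The cost is wording and a redefined comparison, largely on data already planned, with no new patients. The downside is that the comparison within MD rests on a smaller subgroup defined by self-report.
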